### Data analysis

As a mixed-methods approach will be used for the study, two different data analysis approaches will be used. In Phase 1, a qualitative descriptive approach will be used, and in Phase 2, a statistical analysis will be conducted.

#### Phase 1 data analysis

The qualitative data collected during the Phase 1 interviews will be transcribed, coded in two cycles analyzed using a qualitative descriptive approach. The qualitative descriptive approach has been successfully used to interpret and describe a broad variety of perspectives on health interventions. This naturalistic approach recognizes the subjective nature of participants’ preferences and is often incorporated into mixed-methods studies. This approach also supports the co-creation of health messages that relate to the participants’ local cultures and experiences to optimize engagement and support quality improvements, rather than advancing theoretical or conceptual understanding in this phase [11].

#### Phase 2 data analysis

For Phase 2 of the study, descriptive statistics will be collected and reported to compare the two groups. Confounders that will be measured include demographic characteristics of age, education, race group, religion, nationality, employment and earnings. Another confounder that should be balanced is the exposure of participants to Mom-Connect, an online platform that provides mothers with information about maternal and neonatal care. Confounders will be reported by video intervention and treatment as usual (TAU) across rural and urban sites and overall, for the entire cohort (see mock Table 1). Since this is a large enough randomized control trial the confounders should be balanced. We will compare differences between the control and intervention groups in knowledge and intended behavior change at a 3-month follow-up.

**Table 1 Tab1:** Mock table of confounders

Socio-Demographic Variables		Urban			Semi-Rural			Overall		
Variable Groupings	Individual Variables/ Questions	Video Intervention	TAU ANC Brochure	*P*-value	Video Intervention	TAU ANC Brochure	P-value	Video Intervention	TAU ANC Brochure	*P*-Value
	Age									
	Standard/grade									
Race	Race 1									
	Race 2									
	Race 3									
Religion	Religion 1									
	Religion 2									
	Religion 3									
Nationality	Nationality 1									
	Nationality 2									
	Nationality 3									
	Employment									
	Earnings									
	Partnership status									

The outcome variables will also be described overall and by rural and urban sties (see mock Table 2). The reported effect size will be an unadjusted relative risk using Poisson regression. Rates for Poisson regression will be total correct answers divided by total questions. This keeps with the intention to treat paradigm, so questions not attempted or answered as “don’t know” are included as incorrect answers).

**Table 2 Tab2:** Mock table of outcome variables

Variable Groupings	Individual Variables/ Questions	Urban (%)	Semi-Rural (%)	***P***-Value
**Behavioural intentions Mothers**	Attend ANC appointments			
	Own HIV status known			
	Partner HIV status known			
	Take partner to ANC			
	Drink alcohol			
	Wash hands			
	Wear a mask			
	Breastfeed			
	Eat green vegetables			
	Eat fruit			
	Eat meat			
	Take partner to birth			
	Feel fetal kicks			
	Vaccinate child			
	Hold baby			
**Behavioural intentions Partners**	Go to ANC visit			
	Physically enter ANC			
	Pay ANC costs			
	Remind about ANC			
	Ask about ANC			
	Own HIV status known			
	Partners HIV status known			
	Discourage alcohol			
	Encourage wash hands			
	Encourage wear a mask			
	Encourage breastfeeding			
	Provide green vegetables			
	Provide fruit			
	Provide meat			
	Attend birth			
	Encourage fetal kick feel			
	Take vaccination			
	Encourage hold baby			
**Knowledge Score**	Skin to skin KMC			
	Breastmilk prevent infections			
	Breastmilk alone			
	Breastmilk and water			
	Formula feeding			
	Traditional tea/muti			
	Avoid alcohol			
	Source of iron			
	Enough iron			
	Cows milk			
	Postnatal care			
	Condom			
	HIV medication			
	HIV positive breastfeeding			
	Stop breastfeeding			
	Vaccines protect			
	Dangerous vaccines			
	Difficulty sleeping			
	Severe headaches			
	Baby kicks			
	Bleeding			
	Newborn loose weight			
	Newborn fever			
	Cries a lot			
	Black stools			
	Visit clinic			
	Excercise			
	Solid foods			
**User Satisfaction**	Easy to understand			
	Useful			
	Difficult to watch			
	Download easy			
	Download time			
	Follow information			
	Identify with characters			
	All information needed			

Results will be reported by comparing video intervention arm and treatment as usual across rural and urban sites and by outcome sub-groupings (see mock Table 3). Statistical significance will be set at 5% and results will be presented with 95% Confidence Intervals. A Fisher’s exact *P*-value will be reported for all associations.

**Table 3 Tab3:** Mock table of results reporting

Outcome Analysis	Urban				Semi-rural				Overall			
Variable Groupings:	Video Intervention	TAU ANC Brochure	RR (95%CI)	*P*-value	Video Intervention	TAU ANC Brochure	RR (95%CI)	*P*-value	Video Intervention	TAU ANC Brochure	RR (95%CI)	*P*-Value
Behavioural intentions Mothers												
Behavioural intentions Partners												
Knowledge Score												
User Satisfaction												

Relative Risk calculated using Poisson Regression (rate of correctly answered questions over total questions)

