#### Phase 2 sampling & data collection

During Phase 2 of the study, the randomized control trial, researchers and research assistants will randomly recruit women attending an antenatal care visit and their partners, inviting them to participate in the randomized control trial. Every participant will be required to provide informed consent before they can be included in the sample. Participants will be randomized into either the intervention group or the control group until the sample size of 420 has been reached. To implement the randomization, a table with the generated randomization sequence will be used, and as a participant agrees to participate in the study, they will be sequentially allocated to a row in the table that will determining the group that the participant will form part of. The sample size for the randomized control trial, was determined using the primary outcome of the study, change in knowledge. We will allocate participants equally to the treatment and control groups, through a balanced computer-generated random sequence. We use a 0.05 level of significance (*P* < 0.05) and a power of 0.9 with a two tailed test for significance.

Our hypothesis is that at the 3-month follow-up, participants in the control group will score 43% on the intention to change behavior score (12 points out of 28 points in the survey). We propose that after the 3-month follow-up the intervention group will score 61% (17 out of 28 points). This is an 18% absolute increase and a 1.41 times relative increase. A sample size of *n* = 140 was calculated for the intervention group and the control group. We then used an increase of 50% to account for potential participant drop-outs, bringing the sample size for the intervention group to *n* = 210 and the sample size for the control group to n = 210, spread equally and randomly across the two sites (Kgabo CHC[urban site] and Ga-Rankuwa[rural site]). Thus, a total of *n* = 420 participants for the entire randomized control trial will be required. These sample size calculations were carried out on G-Power 3.1.9.6.

Sample size calculations were based on the difference between two independent proportions using a z-test (Power: 0.9, Alpha 0.05, Allocation N1/N2: 1, p1 = 0.43, p2 = 0.61). The sample size per group was rounded up to the nearest 10 patients (N1 = 140, N2 = 140).

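### For the score rows of Table 3, a Fisher's exact P-value on pooled answers overstates significance, and a Poisson interval without person-level variance has the wrong width in either direction

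*Protocol article*

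**What the plan says.** Three statements in the protocol article's section on Phase 2 data analysis work together.

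- The effect size is an unadjusted relative risk from Poisson regression, and "Rates for Poisson regression will be total correct answers divided by total questions". Items left blank or answered as unknown count as incorrect.
- On P-values, a Fisher's "exact *P*-value will be reported for all associations".
- Table 3 has rows for mothers' intentions, partners' intentions, Knowledge and User Satisfaction. Each row has a column for the relative risk with 95% CI and another for a P-value. The footnote repeats the unit of analysis: "Relative Risk calculated using Poisson Regression (rate of correctly answered questions over total questions".

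Under Phase 2 sampling and data collection, participants are randomized one by one. A mother answers 15 intention and 30 knowledge questions, and a partner answers 18 and 30. Knowledge is the primary outcome. The section names no robust, overdispersed or clustered variance.

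**The concern.** The people are randomized, but the stated rate counts answers. One person contributes 15 to 30 answers to a score, and a well-informed respondent tends to get many of them right, so those answers are not independent.

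Fisher's exact test needs independent units. The only 2x2 table whose ratio equals the relative risk in the footnote is correct versus incorrect answers by arm. That table treats one woman's 30 answers as if they came from 30 women.

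Model-based Poisson regression has a different fault. It sets the variance of a person's total equal to its mean, which is right only at one particular within-person correlation.

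P-value and interval would also come from different procedures, so one row of Table 3 could show a significant P-value beside an interval that includes 1. What is at stake is the 5% error rate and the 95% coverage for the primary outcome.

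**Working it through.** **The plan's own figure.** The sample size is the only related calculation: "Sample size calculations were based on the difference between two independent proportions using a z-test", with inputs "Power: 0.9, Alpha 0.05, Allocation N1/N2: 1, p1 = 0.43, p2 = 0.61". The pooled formula is n = [z_a·√(2·0.52·0.48) + 1.2816·√(0.43·0.57 + 0.61·0.39)]² / 0.18².

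- Two-sided (z_a = 1.960): 159.8, so 160 per arm.
- One-sided (z_a = 1.645): 130.1, so 131, which rounds up to the stated 140.

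The article states "a power of 0.9 with a two tailed test for significance", so 140 is not reproduced as described. That is a separate matter. Here 140 serves only as the arm size in a simulation, and the formulas below do not depend on it.

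**Inputs.**

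- m = 30 knowledge questions (article). Table 2 lists 28 knowledge items; m = 28 is checked below.
- p = mean proportion correct on knowledge. Not given. Assumed 52%, 70% and 80%. The 52% is the midpoint of 43% and 61%, which the article gives for the intention score, so it is illustrative only.
- ICC = correlation between two answers from one person. Not given. Assumed 0.02 to 0.15.

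**Variances of one person's total.**

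- True: m·p(1−p)·D, with D = 1 + (m−1)·ICC
- Assumed by a pooled-answer 2x2 test: m·p(1−p). Ratio true/assumed = D
- Assumed by model-based Poisson: m·p. Ratio = (1−p)·D

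Actual two-sided error at nominal 5% = 2·[1 − Φ(1.96/√ratio)].

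**Results, m = 30.**

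| ICC | D | Pooled-answer test | Poisson, mean 52% | Poisson, mean 70% | Poisson, mean 80% |
|---|---|---|---|---|---|
| 0.02 | 1.58 | 12% | 2.4% | 0.4% | <0.1% |
| 0.05 | 2.45 | 21% | 7.1% | 2.2% | 0.5% |
| 0.10 | 3.90 | 32% | 15% | 7.0% | 2.6% |
| 0.15 | 5.35 | 40% | 22% | 12% | 5.8% |

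Worked entry, ICC 0.10: D = 1 + 29·0.10 = 3.90, and 1.96/√3.90 = 0.992, giving 32%. Poisson at 52%: 0.48·3.90 = 1.87, and 1.96/√1.87 = 1.43, giving 15%.

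With m = 28, D at ICC 0.10 is 3.70 and the pooled-answer error is 31%, so the item count hardly matters.

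**Break-even for Poisson.** Setting (1−p)·D = 1 gives ICC = p / [(1−p)(m−1)]. At 52% this is 0.52/(0.48·29) = 0.037; at 80% it is 0.80/(0.20·29) = 0.138. Below break-even the interval is too wide, above it too narrow.

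**What the ICC means on the score scale.** Person-level SD = √[p(1−p)·D/m]. At mean 52%, ICC 0.05 gives 14 points and ICC 0.15 gives 21 points.

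**Simulation check.** Beta-binomial scores under the null, 140 per arm, 4,000 runs, with a continuity-corrected z-test on pooled answers standing in for Fisher. At m = 30, mean 52%, ICC 0.10: pooled 31.2%, Poisson 14.7%, robust Poisson 4.6%. Over all settings run (15 or 30 items, means 43%, 52% and 80%, ICC 0 to 0.20) robust Poisson stayed between 4.4% and 5.8%.

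**The case against.** **The variance may be settled elsewhere.** The article does not say that model-based variance will be used; unadjusted most naturally means without covariates. The analysis plan is not shown and could specify robust variance. This stands: the Poisson part is conditional. Robust variance would repair the interval, but not a P-value that the article assigns to Fisher's test for all associations.

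**Fisher's test can be run on people.** It could be applied to a dichotomised score or to the full score-by-arm table, and a sample size based on proportions of people fits such a reading. But no cut-off or score-by-arm test is stated, and neither would test the relative risk defined in the footnote. The test is sound for categorical baseline variables and for single items with one answer per person.

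**A reader might infer that both procedures are anti-conservative for the primary outcome.** The documents do not support that. The direction for Poisson depends on the mean and the ICC, and neither is given for knowledge. Figures computed at 43% would use the expected control mean of the intention score (12 of 28 points), not of the 30-question knowledge score.

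**The planned effect is large.** With a person-level SD of 21 points and 140 per arm, an 18-point difference has z = 18 / (21·√(2/140)) = 7.2, so a correct test would still be clearly significant. This is fair: the error matters when the true effect is small or absent, which is the case the 5% rate is meant to control.

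**Conclusion.** The rule is wrong as written for the score rows of Table 3.

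- **P-value.** Applied to the stated rate, Fisher's test is anti-conservative for any positive within-person correlation. This needs no assumption about the mean. The size, 12% to 40% for 30 items, rests on assumed ICCs of 0.02 to 0.15.
- **Interval.** If the Poisson variance is model-based, which the article leaves open, the width is wrong in a direction that cannot be fixed from the documents.
- **Agreement.** Taking the two from different methods lets them contradict each other.

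The single-item and categorical baseline uses of Fisher's test are not affected.

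**What to change.** For every score row of Table 3, use one record per participant: number correct as the outcome, log of questions asked as the offset, and arm as the only term. This keeps the unadjusted relative risk. Fit the Poisson model with a robust (sandwich) variance and take both the 95% CI and the P-value from it.

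The variance must be computed by person. A sandwich on answer-level rows without clustering would only return the pooled-answer variance. Where mothers and partners share a row, as the single Knowledge row suggests, cluster on the couple.

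Limit Fisher's exact test to categorical baseline variables and to single items with one answer per person.

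The cost is a sentence in the analysis section and a software option, with no change to data or design. The downside is an interval wider than the model-based one if the ICC exceeds the Poisson break-even, about 0.04 at a mean of 52% and 0.14 at 80% for 30 items. No revised sample size can be derived, because the article gives neither a score SD nor an ICC.

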Expectant mothers assigned to the intervention group will watch the 10 Amandla Mama videos and their partners will receive the same 10 Amandla Mama videos via the social media platform, WhatsApp or short messaging service (SMS). The expectant mothers will be asked to provide the researchers with their contact details and the contact details of their partners. Partners who agree to participate in the study and who provide informed consent will receive the Amandla Mama videos by SMS or WhatsApp. The control group will receive existing treatment as usual-antenatal care only.

After 3 months, knowledge, behavioral intent, and user satisfaction surveys will be administered telephonically to all participants. The follow-up is conducted after 3 months to test long-term retention providing a better predictor for ongoing change. The research assistants under supervision of the researchers, will administer the telephonic survey. Data collected from participants who discontinue with or deviate from the study will not be used.

Surveys for the expectant mothers consist of a total of 61 questions: 10 background questions, 15 behavioral intention questions, 30 knowledge questions and 8 user satisfaction questions (refer to Additional file 1: Annexure 2). Surveys for partners consist of a total of 63 questions: 8 background questions, 18 behavioral intention questions, 30 knowledge questions and 8 user satisfaction questions (refer to Additional file 1: Annexure 3). The user-satisfaction questions, which consider how satisfied the participants are with the Amandla Mama videos, will only be administered to participants in the intervention group. All Phase 2 study participants will receive ZAR 100 to compensate them their time and expenses incurred by participating in our study.

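### Questions not attempted count as incorrect under an intention-to-treat label, with no limit to questions actually put, while the sample size and discontinuation text take drop-outs out of the analysis

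*Protocol article*

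**What the plan says.** Under Phase 2 data analysis, the rate for the Poisson regression is total correct answers over total questions. The article adds: "This keeps with the intention to treat paradigm, so questions not attempted", together with don't-know answers, are counted as incorrect. The rule is worded for questions. It does not say whether a question must have been put to the participant, and it does not mention a participant with no survey.

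Under Phase 2 sampling & data collection, the outcome comes from one contact: "After 3 months, knowledge, behavioral intent, and user satisfaction surveys will be administered telephonically to all participants". The same section sizes the trial at 140 per group and continues: "We then used an increase of 50% to account for potential participant drop-outs", which gives 210 per group. It also says that data from participants who discontinue or deviate are not used.

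Knowledge is the primary outcome and intended behaviour the secondary one; the rule scores both.

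**The concern.** A question can go unanswered for two different reasons. The participant may have been asked and been unable or unwilling to answer; counting that as incorrect is a reasonable scoring choice. Or the question was never put, because the call was not answered or broke off; that says nothing about knowledge. The rule covers both. Intention to treat, the reason given, means analysing people in the group to which they were randomised. It does not require an unobserved outcome to be set to failure.

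The sampling section treats the same people differently. Adding 50% for drop-outs makes sense only if the lost leave the analysis and 140 remain, and discarding discontinuers' data is also exclusion. So a participant never reached could enter the primary analysis with a score of 0 or not at all, and no sentence settles which.

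The risk is bias. Only the intervention arm receives study content, so the arms could differ in how many take the 3-month call. Under zero scoring, that difference would be reported as a difference in knowledge.

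**Working it through.** **Inputs from the article.** "Power: 0.9, Alpha 0.05, Allocation N1/N2: 1, p1 = 0.43, p2 = 0.61"; "a power of 0.9 with a two tailed test for significance"; 140 per group before and 210 after the drop-out increase. The 43% and 61% are stated for the intention score; I use them as planning values for the knowledge score too.

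**Assumed inputs, not in the documents.** Response rates averaging about two thirds, 10 or 5 percentage points apart between arms; SD of responders' scores 0.15 to 0.20.

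**1. The plan's own figures.** 140 × 1.5 = 210, and (210 − 140)/210 = 70/210 = 33.3%. That is the planned allowance, not a ceiling on loss. The 140 does not reproduce: the two-sided z-test for 0.43 versus 0.61 at 90% power gives 160 per group. A one-sided test gives 131, which rounds up to 140. That is a separate matter.

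**2. A broken-off call.** Stopping after 15 of 30 knowledge questions with 61% of those correct scores 15 × 0.61/30 = 30.5% over total questions, against 61% over questions put. The score is halved, not zero. Only a break before the first knowledge question gives 0 for knowledge.

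**3. Unreached participants scored 0: the estimate.** Let r be the response rate and m the mean score among responders. The arm mean is r × m, so

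RR = (m_video/m_control) × (r_video/r_control).

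- Equal response of two thirds: 0.43 × 2/3 = 0.287 and 0.61 × 2/3 = 0.407. The ratio is 1.42, the same as 0.61/0.43.
- No true effect, response 71.7% versus 61.7%: 0.717/0.617 = 1.16, or 0.86 with the arms reversed.
- No true effect, response 69.2% versus 64.2%: 0.692/0.642 = 1.08, or 0.93 reversed.
- True ratio 1.42 with the 10-point gap: (0.61 × 0.617)/(0.43 × 0.717) = 1.22, or (0.61 × 0.717)/(0.43 × 0.617) = 1.65.

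**4. Type I error under zero scoring.** The person-level variance is v = r(s² + m²) − (rm)², with s the SD among responders, m = 0.43 in both arms and 210 per group. SE = √[(v1 + v2)/210], tested two-sided at 5%.

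| Response | s | Spurious difference | SE | Type I error |
|---|---|---|---|---|
| 71.7% v 61.7% | 0.15 | 0.0430 | 0.0230 | 46% |
| 71.7% v 61.7% | 0.20 | 0.0430 | 0.0253 | 40% |
| 69.2% v 64.2% | 0.15 | 0.0215 | 0.0231 | 15% |
| 69.2% v 64.2% | 0.20 | 0.0215 | 0.0254 | 14% |

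**5. Power under the same model.** With 0.43 versus 0.61, one third scored 0 in each arm and 210 per group, the difference is 0.12. The SE is 0.0271 (s = 0.15) or 0.0290 (s = 0.20), and power is 99.3% or 98.5%. At s = 0.30 it is still 94.1%.

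**The case against.** The strongest reply is that the rule concerns questions. Naming unattempted questions alongside don't-know answers most naturally describes blanks within a survey that took place. Read with the drop-out inflation and the discarding of discontinuers' data, the plan could be coherent: people who drop out are not analysed, and blanks from people who were interviewed are incorrect. That reading is available, and the text does not state that an unreached participant scores 0. But the rule has no such limit, and its intention-to-treat justification pulls towards including everyone randomised. Even on the narrow reading, questions never reached in a cut-off call are scored as ignorance.

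A reader might also infer a loss of power: treating each person as one yes/no outcome, the z-test gives 85.8% with 140 per group after exclusion and 73.5% with 210 after zero scoring, against 90% stated. The documents do not support that as a consequence of this rule. The outcome is a score over many questions, and the score model keeps power above 98% at the SDs used here. The gap from 90% to 85.8% arises because 140 does not follow from the two-sided inputs.

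Nor should one say that a third of participants have two opposite scores. A third is a planning allowance, and the alternatives are 0 or no score.

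It is fair to add that the bias figures rest on assumed response gaps, and that imputation details may sit in an analysis plan not shown. The scoring rule, however, is stated in the article.

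**Conclusion.** The point holds as a defect in a stated scoring rule for the primary outcome, and as a disagreement between two sections. A broken-off call gives a deflated score. A never-reached participant scores 0 on one plausible reading and is left out on the other.

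The consequence is bias when response differs between arms: under the assumptions above, a 10-point gap gives a false-positive rate eight to nine times the nominal 5%, and a 5-point gap roughly three times. With equal response the relative risk is unaffected. The change should be made before follow-up data are seen, because otherwise the choice between the two readings could be made with response by arm already known.

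**What to change.** In Phase 2 data analysis, limit the rule along these lines: questions put to the participant and refused or answered don't know count as incorrect; questions not put, because there was no interview or it was broken off, are missing and not incorrect. A participant with no interview then has no score. For a broken-off call, the denominator becomes the number of questions put.

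Reconcile this with the drop-out inflation and the discontinuation sentence in Phase 2 sampling & data collection, so that all three describe the same analysis set. Report the number interviewed by arm. Keep all-zero scoring of the non-interviewed only as an extreme-case sensitivity check.

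The cost is a few sentences and a survey field separating asked-but-unanswered from not asked; no extra participants are needed. The downside is that the primary analysis then assumes the non-interviewed are missing at random, which the interview counts by arm and the sensitivity check help the reader to judge.
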